### Randomization, allocation and blinding

Participants will be randomly assigned to one of the two treatment arms in a 1:1 ratio with stratification according to age (7–12 years; 13–21 years; and 22–50 years). The allocation sequence is a permuted-block randomization and has been generated by an external consultancy (Datamanagement, Public Health and Quality Improvement, Central Denmark Region, Aarhus, Denmark). Participants will be assigned to the intervention by delegated study staff via an online randomization module in an electronic Case Report Form (‘TrialPartner’, Datamanagement, Denmark). The allocation is concealed to the investigative staff and sponsor throughout the study, and unblinding will only occur in the event of a Suspected Unexpected Serious Adverse Reaction or if otherwise required for patient safety.

A hospital pharmacy (Apotheek Haagse Ziekenhuizen, The Hague, The Netherlands) is responsible for preparation of the trial medication. Azithromycin tablets bought from a pharmaceutical company are repackaged and identical placebo tablets are specifically manufactured by the hospital pharmacy. Blinded labelling and packaging of the trial medication in identical blister packages in carton boxes is performed centrally at the hospital pharmacy according to Good Manufacturing Practice. Adherence to the trial treatment will be assessed by participant/parent report and count of returned trial medications.

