### Data collection

Participants will be screened for eligibility in a stable state after having given informed consent to participation. At screening, demographic information (age, gender, ethnicity) will be recorded and inclusion- and exclusion criteria review will be performed, including data on medical history, current symptoms and concomitant medication, physical examination, pregnancy test, electrocardiogram, spirometry, and sputum microbiology. The QOL-PCD [23] will be completed by participants both one week prior to screening and again at the screening visit to obtain baseline values. Screening will be followed by a run-in period of one month to ensure that participants have stable lung function (defined as maximal decrease in FEV_1_% predicted of 10 percentage points from the screening visit to the randomization visit) and that prohibited medications are washed out at randomization. Participants will be withdrawn prior to randomization if they have an exacerbation or receive systemic or inhaled antibiotics at the screening or randomization visit, or if they have received antibiotics for more than 2 weeks during the run-in period. Participants will be reviewed every two months during the 6 months treatment period. Participants will be asked to contact the trial site at the onset of an exacerbation, if possible, and exacerbations will be reviewed at extra visits or by telephone contact. Withdrawal of participants during the trial will occur if the participants fulfil any of the exclusion criteria or due to safety reasons. A QOL-PCD will be completed by the participants, as a follow-up assessment 2 months after the end of the treatment period.

All data will be recorded in an electronic case report form. The primary and secondary outcome measures (see below) are collected at the specified time points. All adverse events occurring from the first administration of the trial medication to the end of the last trial visit will be recorded and monitored (Table 2).

**Table 2 Tab2:** Time and events schedule

	Screening	Treatment period				Follow-up
	Visit *0 months*	Visit *1 month (+2 weeks)*	Visit *3 months (+/- 1 week)*	Visit *5 months (+/- 1 week)*	Visit *7 months (+/- 1 week)*	*9 months*
Informed consent	X					
Demographics	X					
Inclusion/Exclusion criteria review	X					
INTERVENTION:						
Randomization		X				
Azithromycin/Placebo						
Adherence			X	X	X	
ASSESSMENTS:						
QOL-PCD	X	X	X	X	X	X
Patient interview	X	X	X	X	X	

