### Sample size

The planned number of participants to be enrolled in the trial is 125. The sample size is calculated based on the primary endpoint and has been estimated based upon detecting a 50 % reduction in number of exacerbations (assuming a mean of 2.5 exacerbations per year in the placebo group) in the azithromycin group with a statistical power of 90 % and assuming Poisson distribution. On this basis, a sample size of 100 participants completing the trial will be required, with 50 participants in each treatment arm. Allowing for a dropout rate of 20 %, the total number of participants to be enrolled in the trial is 125. Power is 70 % to detect a difference of 5 percentage points between treatments in the pre- to post-intervention change in FEV_1_ % predicted (assuming a SD of 10 % for intra-subject change); and power is 88 % to detect a difference of 5 percentage points in the pre- to post-intervention change in LCI (assuming a SD of 8 % for intra-subject change). Calculations of power are based on two-sided testing with an alpha level of 0.05.

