### Statistical analysis

Two analysis populations are defined: Intention-to-treat population and per-protocol population. All participants who are randomized will be included in the intention-to-treat population analysis, and all available data from drop-outs will be included in this intention-to-treat analysis. The per-protocol population analysis will include all participants, who are randomized, have completed the trial, have not been discontinued from treatment, and have had no major protocol deviations. A participant will be considered to have completed the trial if he or she has completed all the five visits. The per-protocol population will be determined prior to unblinding.

Data will be summarized descriptively. For continuous variables, descriptive statistics such as mean and SD, or median and range (depending on normality) will be summarised. For categorical variables, the frequency will be presented. Analysis of the primary and secondary outcomes will be based on the intention-to-treat population and will be repeated based on the per-protocol population. The primary outcome will be analysed using Poisson regression, with adjustment for age as a potential confounder. The continuous secondary outcomes will be modelled using a linear mixed model including a fixed time-specific treatment effect and random effects of trial site and person. Additional potential confounders, such as age, can be adjusted by including them in the linear mixed model as fixed main effects. The categorical secondary outcomes will be analysed by McNemar’s test or test of marginal homogeneity, as appropriate. All statistical inference tests will be performed using two-sided testing with a significance level (alpha) of 0.05. No adjustment will be made to the significance level for the multiple statistical comparisons planned as part of the secondary analyses.

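### As written, the secondary mixed model assumes equal correlation between visits 2, 4 and 6 months apart; if correlation falls with time, the SE of the month-1 to month-7 change is understated

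*Protocol article*

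**What the plan says.** The Statistical analysis section of the protocol article describes a linear mixed model for the continuous secondary outcomes, with a fixed treatment effect for each time point and "random effects of trial site and person". It gives no serial correlation, random slope or residual covariance, and it does not say whether the treatment effect is a change from baseline or an arm difference at the visit.

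The Sample size section states power for a "difference of 5 percentage points between treatments in the pre- to post-intervention change in FEV_1_ % predicted", and likewise for LCI, "with 50 participants in each treatment arm". On timing, Data collection says: "Participants will be reviewed every two months during the 6 months treatment period". Table 2 puts randomization at month 1 and the later visits at months 3, 5 and 7. Tests are two-sided at 0.05: "All statistical inference tests will be performed using two-sided testing with a significance level (alpha) of 0.05".

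**The concern.** A person effect with independent residuals allows one correlation for every pair of a person's visits. Four visits give three pairs 2 months apart, two pairs 4 months apart and one pair 6 months apart, and the fitted correlation averages over all six. The powered contrast uses only the 6-month pair. If that pair is less correlated than the average, the model attributes too little variance to the change.

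At stake are the confidence intervals and p-values for the end-of-treatment change in lung function, LCI and QOL-PCD. The section applies 0.05 to each secondary test without multiplicity adjustment, and the Discussion makes evaluating LCI and QOL-PCD as outcome measures an aim of the trial.

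**Working it through.** **Inputs from the protocol article.** 50 completers per arm, SD of change 10 (FEV1) and 8 (LCI), difference 5, two-sided 0.05 (Sample size); visits at months 1, 3, 5 and 7 (Table 2). **Assumed:** the correlation patterns, complete data, large-sample normal tests. The site effect is constant over a person's visits and drops out of the change.

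**1. The plan's own figures.** SE of the between-arm difference in change = SD × √(2/50).
- FEV1: 10 × 0.2 = 2.00; power = Φ(5/2.00 − 1.96) = Φ(0.54) = 70.5% (69.7% by t). Stated: 70%.
- LCI: 8 × 0.2 = 1.60; power = Φ(3.125 − 1.96) = 87.8% (87.2% by t). Stated: 88%.

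Both reproduce, so pre-to-post change is the contrast that was sized.

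**2. What the random-intercept model uses.** With balanced data its variance for one person's change is 2 × (average visit variance − average covariance). With equal variances and correlations ρ2, ρ4, ρ6 at 2, 4 and 6 months:

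ρ̄ = (3ρ2 + 2ρ4 + ρ6)/6, and model SE / true SE = √[(1 − ρ̄)/(1 − ρ6)].

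Actual type I error = 2 × [1 − Φ(1.96 × ratio)].

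**3. Example, AR(1) with 2-month correlation 0.90.** Correlations are 0.90, 0.81, 0.729. ρ̄ = (2.70 + 1.62 + 0.729)/6 = 0.8415. Ratio = √(0.1585/0.271) = 0.765. Model SE = 1.53 against a true 2.00. Type I error = 2 × [1 − Φ(1.499)] = 13.4%.

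**4. Range of assumed patterns** (change SD scaled to 10, true SE 2.00):

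| Assumed truth | Ratio | Model SE | Type I error |
|---|---|---|---|
| AR(1) 0.95 | 0.755 | 1.51 | 13.9% |
| AR(1) 0.90 | 0.765 | 1.53 | 13.4% |
| AR(1) 0.80 | 0.786 | 1.57 | 12.4% |
| AR(1) 0.70 | 0.809 | 1.62 | 11.3% |
| AR(1) 0.50 | 0.859 | 1.72 | 9.2% |
| Person + AR + measurement error (0.810, 0.747, 0.703) | 0.878 | 1.76 | 8.5% |
| Person + AR + measurement error (0.805, 0.774, 0.751) | 0.929 | 1.86 | 6.9% |
| Person + decaying part, 2-month autocorrelation 0.25 | 0.930 | 1.86 | 6.8% |
| Person + decaying part, 2-month autocorrelation 0.10 | 0.973 | 1.95 | 5.6% |
| Random slopes, large | 0.828 | 1.66 | 10.5% |
| Random slopes, medium | 0.889 | 1.78 | 8.1% |
| Random slopes, small | 0.935 | 1.87 | 6.7% |
| Constant correlation | 1.000 | 2.00 | 5.0% |

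The slope rows take person variance 6 and residual variance 1, with the slope adding 2, 1 or 0.5 to the month-7 variance. For the largest, the average visit variance is 7.778 and the average covariance 6.407. The model variance of change is 2 × 1.370 = 2.741 against a true 2 + 2 = 4, and √(2.741/4) = 0.828.

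A stable person share cancels from numerator and denominator of the ratio, so adding one to an AR(1) part does not change the result. Simulation of 20,000 null trials at AR(1) 0.50 gave 9.6%, in line with 9.2%.

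**5. The other contrast.** For the plain arm difference at month 7 with unconstrained visit means, the model variance is (2/50) × average visit variance. With equal variances this is exact: under AR(1) 0.90 both SEs are 2.717, and type I error is 5.0%. If variance grows, as in the slope rows, it is 5.5-6.8%.

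**The case against.** The strongest objection is that the article does not close its list. It says the model is "including a fixed time-specific treatment effect and random effects of trial site and person", and the first word leaves room for a residual covariance. The article is condensed and the SAP is not shown; such detail commonly belongs there. This stands against one inference a reader might draw, that the person effect is the only within-person structure the trial will use. It does not dispose of the point, because the article names a structure, and that structure taken alone implies equal correlation.

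A reader might also infer that the standard error is definitely too small. The documents do not support that:
- No between-visit correlation is given. The Discussion describes chronic but somewhat fluctuating symptoms. Short fluctuation around a stable personal level is close to what a random intercept assumes, and gives about 6-7% in the table.
- A time-specific treatment effect can be read as the arm difference at each visit, whose SE is exact under the conditions in step 5. Change from baseline comes from the Sample size section, not from the model description.

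Nor does the point reach every continuous secondary outcome. Audiometry and inflammatory markers are taken only at randomization and end of treatment; with two visits there is one correlation and nothing to average.

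**Conclusion.** The point holds conditionally, as an inexpensive improvement. With the random-effects structure as written and the treatment effect read as the month-1 to month-7 change, any fall in correlation with time, or differing individual trajectories, makes the SE too small. In the four-visit calculations the SE is 0.76-0.97 of its true value and type I error about 6-14%. With constant correlation there is no inflation.

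The result rests on assumed correlations, complete data, 50 per arm and the change reading of the contrast. It concerns spirometry, plethysmography, N2 MBW and QOL-PCD. The primary Poisson analysis is untouched, and nothing here shows a stated power figure to be wrong.

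**What to change.** For the continuous secondary outcomes measured at three or more visits:
- Use an unstructured within-person covariance across the scheduled visits, with Kenward-Roger degrees of freedom, and keep the site effect.
- Name a fallback for non-convergence: a person intercept plus heterogeneous AR(1), or a robust variance.
- State that the month-7 contrast is the change from baseline.

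The cost is wording and a few parameters. Four visits need 10 covariance parameters instead of 2, so 8 more. Including screening for spirometry (five visits) needs 15 − 2 = 13 more; including screening and month 9 for QOL-PCD (six visits) needs 21 − 2 = 19 more. Intervals become slightly wider. No new data are needed.

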
### Aims

This trial will generate the first evidence-based knowledge on pharmacotherapy in PCD. The main objective is to determine the efficacy of azithromycin maintenance therapy for 6 months on respiratory system exacerbations in subjects with PCD, 7–50 years of age.

The secondary objectives of this trial are to:Determine the efficacy of azithromycin on lung function measured by spirometry, on static lung volumes and airways resistance measured by body plethysmography, and on ventilation inhomogeneity measured by nitrogen multiple breath washout (N_2_ MBW) as a new outcome measure;Assess the efficacy of azithromycin on respiratory, sinus and ear symptoms as measured by new, PCD-specific health-related quality of life outcome measure (QOL-PCD) [23];Determine the efficacy of azithromycin on hearing impairment;Determine the efficacy of azithromycin on sputum microbiology and inflammatory markers;Assess the safety of azithromycin maintenance therapy in PCD.

This study tests the hypothesis that maintenance therapy with azithromycin provides significant improvement in PCD respiratory disease compared to placebo, by reducing respiratory system exacerbations and by improving lung function, ventilation inhomogeneity, health-related quality of life and hearing impairment. Maintenance therapy with azithromycin is expected to be safe with no serious adverse events compared to placebo.

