## Methods/Design

### Study design

This study is a multi-centre, parallel group, double-blind, randomized, placebo-controlled trial with azithromycin maintenance therapy in subjects with PCD (Fig. 1).

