#### Sputum microbiology

Sputum will be sampled at all visits for culture of bacteria and fungi. When the participant cannot cough up sputum voluntarily, then sampling of sputum is performed according to local procedures e.g. by use of cough swabs or by laryngeal suction. Sputum will be cultured for at least the following microorganisms: *Streptococcus pneumonia*, *Group A beta-haemolytic Streptococcus*, *Staphylococcus aureus*, *Moraxella catharrhalis*, *Haemophilus influenzae*, *Pseudomonas aeruginosa*, *Burkholderia cepacia complex*, *Achromobacter xylosoxidans* and *Aspergillus fumigatus*. Microscopy of bacteria will not be performed. During an exacerbation, participants will be asked to deliver sputum samples, which, in addition to regular cultures, will be analysed for respiratory viruses and mycoplasma pneumoniae by polymerase chain reaction. The testing will include the following viruses: Influenza A and B, rhino virus, adenovirus, respiratory syncytial virus, bocavirus, enterovirus, metapneumovirus and parainfluenza virus. Culture incl. antibiotic susceptibility testing and polymerase chain reaction are performed at the local microbiological laboratories.

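### The tests named for the categorical secondary outcomes are paired within-person tests and do not compare azithromycin with placebo

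*Protocol article*

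**What the plan says.** The Statistical analysis section gives each type of outcome its own method. The primary outcome gets an age-adjusted Poisson regression. The continuous secondary outcomes get a linear mixed model with a treatment effect at each time point. For the rest it says: "The categorical secondary outcomes will be analysed by McNemar’s test or test of marginal homogeneity, as appropriate". No between-arm test or treatment term is given for categorical outcomes.

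The design is set out under Study design: "This study is a multi-centre, parallel group, double-blind, randomized, placebo-controlled trial with azithromycin maintenance therapy in subjects with PCD". Allocation is unmatched (Randomization, allocation and blinding): "Participants will be randomly assigned to one of the two treatment arms in a 1:1 ratio with stratification according to age". The hypothesis under Aims is that "maintenance therapy with azithromycin provides significant improvement in PCD respiratory disease compared to placebo".

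The article does not list its categorical outcomes. The clearest candidates are the culture and susceptibility results. Aims includes the objective "Determine the efficacy of azithromycin on sputum microbiology and inflammatory markers", and the Sputum microbiology section says "Sputum will be sampled at all visits for culture of bacteria and fungi". Adverse events are described after these, under the Secondary outcomes heading. Under Data collection their window opens at first dose: "All adverse events occurring from the first administration of the trial medication" onward.

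**The concern.** McNemar's test asks whether a proportion differs between two linked measurements. The test of marginal homogeneity extends it to more than two categories. Participants in the two arms are not linked to each other, so the link can only be before and after within one person. Run within an arm, the test asks whether that arm changed. Run on both arms together, it asks whether the whole trial population changed. Neither is the question under Aims.

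The danger lies in how such results get read. A significant change on azithromycin beside a non-significant one on placebo looks like a drug effect, but it can come from season, regression to the mean after selecting stable patients, or chance. A real effect can also be hidden: if the arms move in opposite directions, the pooled test sees no net change. The outcomes most exposed are sputum culture and emerging macrolide resistance. The first belongs to a stated secondary objective, and the Discussion names resistance as a safety concern.

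**Working it through.** **Inputs from the article.** 50 completers per arm (Sample size), two-sided alpha 0.05 (Statistical analysis), and unmatched 1:1 allocation. The article gives no prevalence, drift or power for any categorical outcome, so there is no planned figure to reproduce. The prevalences and transition probabilities below are assumptions.

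**What the test uses.** Let *b* be the number going from negative to positive and *c* the number going from positive to negative. Exact McNemar compares *b* with a Binomial(*b* + *c*, 0.5). Treatment arm does not enter the statistic.

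**Calculation.** With baseline prevalence π, loss probability p₁₀ and gain probability p₀₁:
- end prevalence = π(1 − p₁₀) + (1 − π)p₀₁
- chance that a person contributes to *c* = π·p₁₀, and to *b* = (1 − π)·p₀₁

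The rejection probability *r* of one arm is the exact sum over these counts with n = 50; the pooled test uses n = 100. The arms are independent, so P(exactly one arm significant) = 2r(1 − r) and P(azithromycin only) = r(1 − r).

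**No drug effect, drift from 50% to 35% in both arms.** p₁₀ = 0.5 and p₀₁ = 0.2 give an end prevalence of 0.5 × 0.5 + 0.5 × 0.2 = 0.35. Then:
- r = 0.355
- exactly one arm: 2 × 0.355 × 0.645 = 0.458
- azithromycin only: 0.355 × 0.645 = 0.229
- pooled: 0.674

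Simulations of 20,000 trials agree (0.36, 0.46, 0.23 and 0.67). A two-sample test of the end-of-treatment proportions rejects in 4.9% of simulated trials.

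**Range over the assumed drift, no drug effect in any row:**

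| Drift in both arms | p₁₀ / p₀₁ | Exactly one arm significant | Pooled test rejects |
|---|---|---|---|
| none (50%) | 0.3 / 0.3 | 5% | 3% |
| 20% to 16% | 0.5 / 0.08 | 8% | 10% |
| 50% to 45% | 0.4 / 0.3 | 11% | 10% |
| 50% to 40% | 0.4 / 0.2 | 29% | 37% |
| 50% to 35% | 0.5 / 0.2 | 46% | 67% |
| 60% to 40% | 0.4 / 0.1 | 39% | 98% |

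In the last row r is about 0.74, so in many trials both arms are significant and exactly one arm is less common. For the fall from 50% to 40%, other transition rates move the figure for exactly one arm between about 25% and 37%.

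**Real drug effect.** Let azithromycin go from 50% to 35% (p₁₀ = 0.4, p₀₁ = 0.1) and placebo from 50% to 65% (p₁₀ = 0.1, p₀₁ = 0.4). The pooled prevalence stays at 50%, so pooled McNemar has nothing to detect. In 20,000 simulated trials it rejects in 2.2%, each within-arm test in about 48%, and a between-arm test in 88%.

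**Adverse events.** Recording starts with the first dose, so the occurrence of an event has no earlier value to pair with. If the sentence is meant to cover event incidence, the named tests cannot be computed before against after.

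**Repeated cultures.** McNemar uses two time points, while sputum is cultured at every visit.

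**The case against.** The strongest reply concerns scope. The primary outcome and the continuous secondary outcomes already have between-arm analyses. The domains that the Discussion puts in focus (exacerbations, lung function, quality of life, hearing) are mostly counts or continuous measures. The sentence therefore governs a residual set of outcomes that did not drive the sample size. That is right, and it limits the consequence: the main efficacy conclusion does not depend on this sentence.

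Second, the list of affected outcomes is inferred. The article does not commit to a significance test of adverse-event incidence; it also plans to present frequencies for categorical variables, and Data collection gives adverse events their own sentence. Some safety measures, such as susceptibility and blood tests, do have a pre-treatment value. The adverse-event point is therefore conditional and concerns incidence only. Tympanometry is performed, but no categorical outcome is defined from it, so it is not relied on here.

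Third, the large error rates need a marked drift in both arms, and the article does not say that within-arm p-values will be set against each other. Both points are fair; with little drift the rates are small. But without that comparison the plan contains no treatment comparison at all for these outcomes.

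Two defences fail. The words 'as appropriate' only choose between two paired tests. And a separate analysis plan would not make the statement right, because the article names a method rather than leaving one open.

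**Conclusion.** The concern holds. As written, the plan tests change over time for the categorical secondary outcomes and does not test azithromycin against placebo. This follows from the design and the nature of the tests, and needs no assumption about data.

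The practical size does need assumptions. With 50 per arm and no drug effect, the chance that exactly one arm is significant runs from about 5% with no drift to about 46% when both arms fall from 50% to 35%. The pooled test rejects in about 3% and 67% of trials in those two cases, and in up to 98% for a fall from 60% to 40%. The upper figures are strong-drift cases. Even where the rates are low, the result says nothing about the treatment contrast.

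The fault is confined to the categorical secondary outcomes, chiefly sputum culture and susceptibility, and to adverse-event incidence if that is to be tested.

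**What to change.** Replace the sentence with a between-arm analysis, before unblinding:

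- **Binary outcomes** such as culture or resistance status: logistic regression of end-of-treatment status on treatment, adjusted for baseline status and age stratum. If all visits are to be used, a mixed logistic model or GEE with treatment-by-visit terms is an option, but it may be unstable for rare pathogens at 50 per arm.
- **Ordered categories**, if there are any: a proportional-odds model with the same adjustment.
- **Adverse-event incidence**, if tested: Fisher's exact test, or a risk difference with confidence interval.

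The text should also list which secondary outcomes are categorical. McNemar's test may stay as a within-arm description, labelled as such. Any valid between-arm comparison would cure the fault; adjusting for baseline keeps the before-and-after information that the paired tests were presumably meant to use. The cost is a change of wording in the statistical section, with no further data or participants.
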